### 9.1. Adverse event reporting

Any adverse event reported by the participant will be captured in the 'adverse event report' form. Information on AE will be collected by the treating physician at each scheduled visit and by the field worker during home visits. Besides scheduled study visits, AEs will be collected through weekly phone reviews. Any participant reporting an AE will be seen by the research clinician at the earliest appointment (depending on the severity). Details of all events including onset date, causality to the study intervention will be reported, treatment given, stop date will be captured in the respective AE report form.

### 9.2. Definition of Serious Adverse Events

An untoward medical event leading to /resulting in any of the following will be considered as "serious adverse event"

- Death
- is life-threatening
- requires inpatient hospitalisation or prolongation of existing hospitalisation
- results in persistent or significant disability/incapacity
- loss of foetal movements or ultrasonographically confirmed foetal death
- 'Important medical events' if they jeopardise the participant or require an intervention to prevent one of the above consequences.

#### 9.2.1. Expected SAE

Expected SAEs include potential medical events (as listed below) will be considered as they are likely to be related to the interventions. These events are therefore **protocol-defined exceptions to SAE reporting**. These events should be captured in the SAE form, but does not require reporting to DMC within scheduled timelines. However, local ethics committees should be informed of such events if the principal investigator believes the event is related to PRIMORDIAL interventions.

- persistent vaginal spotting/bleeding after randomisation
- calf pain/swelling (diagnosed to be related to thrombophlebitis or deep vein thrombosis)
- Dyspnoea at rest
- painful premature contractions
- decreased foetal movements
- preterm labour
- preterm/premature rupture of membranes
- Diagnosis of placenta praevia after 26 weeks of pregnancy
- Pre-eclampsia / Eclampsia

Date and version No: 18th July 2019, Version 4.2

### 9.3. Reporting Procedures for Serious Adverse Events

All research staff will undergo formal GCP training as well as on reporting procedures for AEs and SAEs.

The PI shall report all SAEs without filtration, whether or not related to the intervention, within 24 hours of becoming aware of the event to the Sponsor. If the SAE is related to the intervention, the respective Ethics Committee should be notified within seven calendar days if fatal or life-threatening, and all others within 15 calendar days.

The minimum information required for this initial SAE report is:

- Trial number and (short) title
- Participant's ID
- Date and time of onset
- Description of the event (clinical history, associated signs and symptoms)
- Intervention administered
- Reporter's name

The PI/study coordinator will not wait for additional information to fully document the event before notifying. The report is then to be followed by submission of a completed SAE Report Form as soon as possible, detailing relevant aspects of the SAE in question. All actions taken by the PI and the outcome of the event must also be reported immediately. A decision whether to continue/discontinue the intervention (yoghurt+/- PA) will be made by the treating obstetrician depending on the causality of the event.

For documentation of the SAE, any actions taken, outcome and follow-up, a SAE Report Forms will be used. All follow-up activities have to be reported, if necessary on one or more consecutive SAE report forms in a timely manner. All fields with additional or changed information must be completed and the report form should be forwarded to the respective Ethics Committee within seven calendar days after receipt of the new information. Hospital case records and autopsy reports, including verbal autopsy, will be obtained where applicable.

All SAEs would be reported to the Data Monitoring Committee (DMC) and Oxford Tropical Research Ethics Committee (OxTREC) where in the opinion of the PI the event was 'related' (resulted from administration of any of the research procedures) and 'unexpected' (the type of event is not listed in the protocol as an expected SAE). Reports of related and unexpected SAEs should be submitted within 15 days of the PI becoming aware of the event to DMC and OxTREC.

## 10. STATISTICS AND ANALYSIS

### 10.1. Description of Statistical Methods

We will analyse the study using both (1) the intention-to-treat principle and (2) per protocol, including only those participants adhering to at least 75% of the proposed intervention. In addition, we will run a sensitivity analysis to assess the effect of protocol deviation compared to 100% adherence. Analyses will be performed blinded to the intervention group allocation.

Date and version No: 18th July 2019, Version 4.2

Descriptive analysis of the first 40 participants who complete visit 2 (26-28 weeks) will be performed as advised by the funders (MRC-UK). The analysis is intended to assess feasibility, retention and adherence to all study-related procedures.

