| Planned Study Period                                                          | 36 months                                                                                                                                                                                                                                                   |                                                                                                                                                                                                                                                                                                                                                                                                            |
|                                                                                      | Objectives                                                                                                                                                                                                                                           | Outcome Measures                                                                                                                                                                                                                                                                                                                                                                                    |
| Primary                                                                       | To determine the efficacy of life-style interventions (yoghurt consumption and physical activity), given to pregnant women at high risk of GDM , in reducing the incidence of GDM.                                                                          | Women will be diagnosed to have GDM if one or more plasma glucose concentrations following a 75g OGTT equals or exceeds the following: fasting glucose $\geq 5.1$ mmol/l (92 mg/dl) and/or 1h glucose $\geq 10.0$ mmol/l (180 mg/dl) and/or 2h glucose $\geq 8.5$ mmol/l (153 mg/dl) at 26-28 weeks gestation or if the fasting plasma glucose concentration is $\geq 5.1$ mmol/l at 32 weeks of gestation |

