## 5. STUDY DESIGN

**Design:** 2 x 2 factorial design, multi-centric, open labelled, randomized controlled trial

**Total study duration:** 36 months

**Number of scheduled visits:** 5

- (i) **Screening visit (visit -2,  $\leq 16$  weeks GA):** Singleton pregnant women willing to participate in the study will be assessed for eligibility based on inclusion/exclusion criteria and eligible participants will be asked to sign an informed consent if willing to participate. Eligible women will undergo an oral glucose tolerance test (OGTT) to rule out impaired glucose intolerance or diabetes at screening and will also undergo dating ultrasound scan. Routine antenatal examination will be done. Barriers to life-style interventions-1 during pregnancy will be assessed using a questionnaire.
- (ii) **Run-in visit (visit -1,  $\leq 17$  weeks GA):** Baseline assessments of dairy product consumption will be done using standardized questionnaire. Additionally, objective measurements of baseline PA activity over 7 days will be assessed in all study participants (with the result blinded to participants) using a wearable accelerometer device (Garmin Vivofit 4 fitness band).
- (iii) **Randomization ( $\leq 18$  weeks GA):** Women will be randomized to either (i) diet (consumption of 200g of yoghurt per day), (ii) PA (a minimum of 40% increase above the recorded baseline PA) (iii) diet and PA or (iv) standard care. Active intervention will be from randomization to 32 weeks of GA.
- (iv) **Visit 1 (18-20 weeks GA):** maternal weight, blood pressure, routine antenatal examination and foetal morphology scan.
- (v) **Visit 2 (26-28 weeks GA):** maternal weight, blood pressure, routine antenatal examination and OGTT. Primary endpoint (diagnosis of GDM based on IADPSG criteria) will be assessed at this visit. Women with GDM will continue on allocated study intervention until end of study (week 32) in addition to the clinical management provided as per the local obstetric practice.
- (vi) **Visit 3 (32 weeks GA, End of Study visit):** maternal weight, blood pressure, routine antenatal examination, ultrasound foetal scan and fasting blood glucose and barriers to pregnancy intervention-2 assessment. (A repeat ultrasound scan at this stage is based on the evidence that growth restriction although starts in early pregnancy, is more marked between 22-34 weeks and also that foetal measurements do not have

Date and version No: 18th July 2019, Version 4.2

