## 7.6. Subsequent Visits

### 7.6.1. Visit 1 (week 18-20)

- I. **Weight:** Weight of the mother will be recorded as described in 7.5.1 (II)
- II. **Blood pressure:** Systolic and diastolic BP of the mother will be recorded as described in 7.5.1 (III)
- III. **Antenatal examination (fundal height):** Routine antenatal examination including fundal height will be recorded as described in 7.5.1 (IV)
- IV. **Safety assessments** to interventions (e.g. adverse events and/or SAE assessment).
- V. **Concomitant medication** assessment
- VI. **Compliance assessment:** to interventions (step count, yoghurt diary)
- VII. **Morphology scan:** The following variables would be measured and recorded:  
Gestational age, bi-parietal diameter, head circumference, femoral length, Abdominal circumference, estimated foetal weight, liquor amount, placenta: anterior/posterior and upper segment/lower segment, amniotic Fluid Volume Index, Uterine artery Doppler: Pulsatility Index, Systolic/diastolic ratio, gross anomalies in region of head and neck (transcerebellar plane, transventricular plane, biparietal plane, nose/lips), thorax (lungs, 4 chamber view, outflow tract, diaphragm), Spine, Abdomen (stomach bubble, kidneys, cord insertion, number of vessels in cord, genitalia, limbs). Participants with any foetal congenital anomaly, placental malformation or malposition or abnormal ultrasound features that can compromise pregnancy outcome according to the investigator will be withdrawn from the study at this stage.

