### 7.8.1. Discontinuation/Withdrawal from the study

Discontinuation from the study occurs

- When a participant voluntarily withdraws consent to further participation at any time during the trial.

Date and version No: 18th July 2019, Version 4.2

- Significant protocol deviation such as Ineligibility (either arising during the study or retrospectively having been overlooked at screening)
- Loss to follow-up

Details of withdrawing/discontinuation from the study prior to completion of all scheduled visits should entered in the “study termination form”

Participants who are diagnosed to have GDM (by laboratory evidence within the protocol or outside diagnosis confirmed by an OGTT at study centre) should continue interventions till week 32 (end of study visit), unless there is a safety concern.

Temporary or permanent discontinuation of interventions (as detailed in sections 7.8.1 and 7.8.2) for safety reasons will not lead to withdrawal of the participant from the trial. Withdrawal of the participants will not be replaced by recruitment of new participants. The primary reason for withdrawal will be specified in the Case Report Form.

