## 10.2. The Number of Participants

The sample size is 1856 high-risk women (928 to be recruited in The Gambia and India). The study was powered to have 80% to detect a 33% reduction in the incidence of GDM, for the main effects of diet and PA, with a family-wise significance level of 5% for a two-sided test (i.e. each effect was tested at a significance level of 2.5%). It was assumed that participants could be pooled across centres (no interaction between interventions and country at the 5% level). The sample size was inflated to allow for a 15% drop out rate in each of the four strata, with drop outs defined as non-compliant participants (i.e. no risk reduction in their incidence of GDM).

The effect sizes for the sample size calculation were:

Prevalence of GDM in high-risk pregnant women: The largest study of GDM women (The HAPO study, 25,505 pregnant women unselected for GDM risk at 15 centres in nine countries) reported a GDM prevalence rate, based on IADPSG criteria, of 17.8% among the general population. In our 'high-risk' population, we assume that the prevalence will be higher than in the HAPO study. Therefore, we have estimated the prevalence of 25% in our study.

Estimated risk reduction: A recent meta-analysis (Song et al. Obesity reviews 2016) has shown that either diet or PA results in 18% (95% CI 5-30%) risk reduction in GDM in general pregnant population and interventions as early as 15 weeks of gestational age was also associated with reduced GDM risk (Relative risk: 0.80, 95%CI 0.66-0.97). Putting all these together, we estimate the risk reduction would be higher (about 1/3, 33%) in this high-risk population. We modelled the GDM percentages in four equal-sized combinations of control (c) and treatment (t) arms as 25% (c-c), 16.75% (c-t and t-c) and 11.2 in t-t group. Therefore, in simple comparisons of one exposure, the percentages will be 20.9% vs 13.0%.

Absence of intervention\*country interaction: In order to pool the participants of both countries, we will be assuming that there are no differences between the participants of both countries. This initial test for a non-significant interaction term (at the 5% level) between each intervention and country was also taken into account in the sample size simulation.

The sample size calculation was performed by simulation (in R version 3.5.2) according to the following algorithm:

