### 12.1. DATA SAFETY MONITORING COMMITTEE (DSMC)

An independent Data Safety Monitoring Committee (DSMC) has been set up to review the progress of the trial and provide feedback to the Trial Steering Committee (TSC).

The DMC will be responsible for reviewing

- (i) general study progress (recruitment, compliance, loss to follow-up)
- (ii) clinical study safety data and assess and/or adjudicate all events of deaths
- (iii) the GDM event rate and key secondary/safety outcomes
- (iv) results of the interim analysis. The DSMC includes the following members (To address: chair of DSMC, Report preparation, confirm meeting timelines).

The DMC will review and analyze, on a regular basis, unblinded safety data throughout the study.

An independent DSMC with members who are independent from the Sponsor and the investigators for the PRIMORDIAL study comprises of experts in clinical trials/epidemiology, biostatistics and obstetrics and include the following members

| Name (Designation)                                               | Address                                                                                             | Email                                                        |
|------------------------------------------------------------------|-----------------------------------------------------------------------------------------------------|--------------------------------------------------------------|
| [name]
(Paediatrician & Postdoctoral Research Fellow) | MRC Unit The Gambia at the London School of Hygiene & Tropical Medicine, Fajara, Banjul, The Gambia | [contact]             |
| [name]
(Biostatistician)                         | MRC-LEU, University of Southampton, UK                                                              | [contact] |

Date and version No: 18th July 2019, Version 4.2

|                                     |                                                                      |                                                                          |
|-------------------------------------|----------------------------------------------------------------------|--------------------------------------------------------------------------|
| [name]
(Obstetrician) | Nuffield Department of
Obstetrics and Gynaecology,
Oxford, UK. | [contact] |

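### The feasibility analysis takes only women who complete visit 2, so it cannot measure retention to visit 2 (minor)

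*Protocol*

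**What the plan says.** Protocol section 10.1 describes one early look at the data: "Descriptive analysis of the first 40 participants who complete visit 2 (26-28 weeks) will be performed as advised by the funders (MRC-UK"). Its purpose follows directly: "The analysis is intended to assess feasibility, retention and adherence to all study-related procedures". No denominator of women randomised is named.

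Visit 2 carries the oral glucose tolerance test (OGTT). Section 5 says of it: "Primary endpoint (diagnosis of GDM based on IADPSG criteria) will be assessed at this visit". The Synopsis adds a second route to the same endpoint after visit 2: "or if the fasting plasma glucose concentration is $\geq 5.1$ mmol/l at 32 weeks of gestation".

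The protocol provides for exits between randomisation and visit 2. Under section 7.6.1, women with certain scan findings at visit 1, including "abnormal ultrasound features that can compromise pregnancy outcome according to the investigator will be withdrawn from the study at this stage". Section 7.8.1 lists voluntary withdrawal, ineligibility found later and loss to follow-up. Stopping an intervention is treated differently: temporary or permanent discontinuation "for safety reasons will not lead to withdrawal of the participant from the trial" (section 7.8.1).

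Section 12.1 makes the data safety monitoring committee (DSMC) responsible for reviewing "general study progress (recruitment, compliance, loss to follow-up"), with meetings every six months.

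**The concern.** Retention is a proportion: women still in the study at a given point, divided by women who started. Section 10.1 selects its 40 women on the event being measured, so numerator and denominator for retention to visit 2 are the same people. The protocol does not merely leave a detail open here. It states a population that cannot serve the purpose given in the adjacent sentence.

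What is at stake is feasibility information. The funder would receive a retention figure that is fixed in advance, for the visit at which the main part of the primary endpoint is measured. The same selection affects the count of completed procedures, because any woman lost before visit 2 also missed the OGTT. It could affect the picture of daily adherence as well, if those who left followed the interventions less closely than those who stayed.

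**Working it through.** The protocol derives no figure for the 40, so there is nothing to reproduce. The check concerns the denominator.

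**Inputs.** n = 40, selected on completing visit 2 (section 10.1). True retention from randomisation to visit 2, r, is not given in the protocol and is varied from 70% to 95%. The 85% row echoes the 15% allowance in section 10.2, but only as an illustration, because that allowance is defined as non-compliance (see the objection).

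**Retention.** Reported retention = 40/40 = 100% for every r. The expected number randomised to yield 40 completers is 40/r, and the number uncounted is 40/r − 40.

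| True r | Randomised (40/r) | Uncounted | Reported |
|---|---|---|---|
| 95% | 42.1 | about 2 | 100% |
| 90% | 44.4 | about 4 | 100% |
| 85% | 47.1 | about 7 | 100% |
| 80% | 50.0 | 10 | 100% |
| 75% | 53.3 | about 13 | 100% |
| 70% | 57.1 | about 17 | 100% |

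Taken at face value, 40/40 has an exact 95% lower bound of 0.025^(1/40) = 91%. It would therefore appear to exclude 85% even if 85% were true. A set defined at randomisation is informative: 40 of 47 gives 85% (exact 95% CI 72% to 94%), and 34 of 40 gives 85% (70% to 94%).

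**Completion of the visit 2 OGTT.** It is 100% in the 40 and r in all randomised women, so the overstatement is 1 − r, or 15 points at r = 85%.

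**Yoghurt and step-count adherence.** Adherence in all randomised women = r × A(completers) + (1 − r) × A(leavers). Neither A is in the protocol. Assume 80% in completers and r = 85%:

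- Leavers 0%: 0.85 × 80 + 0.15 × 0 = 68%, overstated by 12 points.
- Leavers 40%: 68 + 0.15 × 40 = 74%, overstated by 6 points.
- Leavers 80%: 68 + 0.15 × 80 = 80%, no bias.
- Leavers 90%: 68 + 0.15 × 90 = 81.5%, understated by 1.5 points.

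With leavers at 0%, the overstatement runs from 4 points (r = 95%) to 24 points (r = 70%). The direction depends on an assumption about leavers that the documents do not settle.

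**The case against.** The strongest reply is that the 40 may be meant only as a timing trigger: report once 40 women have reached visit 2, counting everyone randomised by then. The stated aim of assessing retention favours that reading, and the funder's own specification is not shown. However, the text describes an analysis of those 40, not an analysis when 40 have completed. If a trigger was intended, the same sentence needs the same edit.

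Other parts of the reply stand and limit the point. Each of the following is a stronger reading that a reader might infer but that the documents do not support:

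- *That this is the only early look at losses.* The DSMC reviews compliance and loss to follow-up every six months (section 12.1). That does not alter the population of the funder's check, but it means losses are not invisible.
- *That the 15% allowance in the sample size goes untested.* Section 10.2 allows for a "15% drop out rate in each of the four strata, with drop outs defined as non-compliant participants". In its simulation these women keep an outcome, at the control-group rate. Such women can complete visit 2 and be among the 40.
- *That no adherence problem could show.* Women who stop an intervention for safety reasons stay in the trial (section 7.8.1), follow-up continues after permanent discontinuation (section 7.8.2.2), and step counts and yoghurt diaries are reviewed at visits 1 and 2. Poor adherence among completers would be visible.
- *That early completers are mainly late entrants.* The protocol gives only upper gestational limits for entry and no distribution, so neither the size nor the consequence can be shown.

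**Conclusion.** The point holds, and it is minor. Followed as written, the feasibility analysis returns 100% retention to visit 2 at any true retention. This needs no assumption beyond the wording of section 10.1. At an assumed true retention of 85%, about 7 of 47 randomised women go uncounted, and completion of the visit 2 OGTT is overstated by the same 15 points. Overstated yoghurt or step-count adherence is possible but not established, because it rests on assumed values for women who leave. Some exits, such as withdrawal after the visit 1 scan, need have nothing to do with adherence.

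Retention from visit 2 to week 32, where the fasting glucose part of the endpoint is measured, is not fixed by this selection. The analysis is descriptive and carries no go/no-go rule. A reader might infer that it threatens the trial's conclusions, but the primary analysis and its error rate are not affected.

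**What to change.** Change the sentence in section 10.1 so that the set is defined by randomisation. Either option works:

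- the first 50 or so consecutively randomised women, analysed once all of them have passed 28 weeks; or
- 40 visit 2 completers as the timing trigger only, with the analysis including all women randomised long enough ago to have passed 28 weeks.

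Report retention as visit 2 OGTT done divided by women randomised, and adherence over the same denominator.

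The cost is one sentence and no new data collection. The report may come a few weeks later and may show a less favourable figure.
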